### 2.1.1 Recruitment

Study recruitment will begin in August 2024 and be completed in three ways: (1) by teachers using approved scripts during school home visits, (2) by the research team during parent/school open house events, and (3) through materials distributed through backpacks during the first month of school. Students will be enrolled on a first-come, first-served basis. If we have recruited 90 children, recruitment will end, and no additional students will be enrolled.

### 2.2. MAP e:Health

#### 2.2.1. Theoretical underpinnings

Motor Skills at Playtime (MAP) is a high-autonomy intervention designed to be implemented within the established gross motor opportunities in schools [45]. MAP is rooted in Achievement Goal Theory [39, 65–67] and is delivered through a pseudo-mastery motivational climate. Specifically, a full mastery climate includes six specific components or structures commonly known as the TARGET structures (task, authority, recognition, grouping, evaluation, and time) [67] (see Table 1). MAP implements four of the six target structures (task, authority, grouping, and time) [45]. The two structures not included (recognition and evaluation) were removed to (1) increase the sustainability and scalability of the program and (2) fit within the m:health modality. This removal is key as we are asking teachers and schools to facilitate, not implement, the program; however, by removing these structures, we recognize we can no longer claim this program as a mastery-motivation climate. Therefore, we have termed this particular implementation as a pseudo-mastery climate. See Table 1 for a full description of the TARGET structures and their application and examples of application in MAP.

**Table 1 pone.0308047.t001:** TARGET Structures and their Inclusion in MAP m:health.

Structure	Conceptual Definition	Inclusion in MAP m:health	Example
**T**ask	Design movement tasks and instructional activities to encompass a variety of levels	All activities are designed to incorporate a minimum of three levels of difficulty (e.g., easy, medium, or hard). The videos include a full verbal description of easy and hard activities and invite participants to “choose the easy [insert name of skill], hard [insert name of skill], or something in the middle”.	Audio included on instructional video: “It’s simple to make throwing easier or harder. It is easier to throw at big targets or targets that are close to you. It is harder to throw at small targets or targets that are far away from you. So you can choose. Do easy throws, hard throws, or something in the middle. Choose what is right for you.”
**A**uthority	Shared decision making. Children actively participate in the instructional process	Motor skills are added to the extant gross motor play. Children have authority in how they play during that time. We also encourage teachers to include children when selecting the session number for the day.	Ask the children if they want to do session 1 (throw and run) or session 3 (throw and gallop).
**R**ecognition	Feedback/praise is provided individually and in private	Not included	Not included
**G**rouping	Self-selection of peer interactions	Motor skills are added to the extant gross motor play. Children have the authority to select what peer(s) they play with or if they play by themselves.	Have the children self-select peer groups during extant gross motor play.
**E**valuation	Self- or individual standards for progress	Not included	Not included
**T**ime	Flexibility in schedules; flexible pace of learning	Motor skills are added to the extant gross motor play. Children have the authority to select where they spend their time during the play period.	Children can select to play with MAP stations or continue to play without them. Teachers will report back daily on if the children did or did not play with MAP stations.

#### 2.2.2. Components of e:MAP

The e:MAP program contains two distinct parts: (1) instructional videos and (2) motor skill activities.

Children will view instructional videos in their classrooms prior to engaging in their established gross-motor playtime at the school. This time is typically outdoor recess or free play in a large gym or open space if the weather inhibits outdoor play. The instructional videos contain all instructional elements of the program and are delivered electronically through a private YouTube channel. These videos adhere to tenents of Achievement Goal Theory, such as including a description of how to self-modify the FMS tasks based on the needs of the learners and peer-modeling [67]. In total, there are 48 videos that are classified to the user as sessions. Users are given a suggested order to view the sessions but can self-select their own sessions if they prefer. Each session video is approximately 3 minutes in length and includes a video with two motor skills (one locomotor skill and one object control skill). The skills are first introduced and explained by an adult, and then three skill demonstrations are provided. The first skill demonstration is of the adult correctly executing the skill. The second and third demonstrations are of a preschool-aged boy [5 years] and a girl [3 years]. The order of the child demonstrations is randomly assigned as to which child demonstration is presented first. After the completion of the demonstrations, the user hears an explanation and sees visual prompts on how to adjust the skill practice to make it easier or harder (task of the TARGET structures). The overall user experience within each session was designed to adhere to effective design features within e:health interventions (see Table 2) [68].

**Table 2 pone.0308047.t002:** Design Features Associated with Effective e:health Interventions^57^ and their Inclusion in MAP m:health.

Feature	Inclusion and Examples in MAP m:health
Social context and support	All videos include recordings of a person speaking to the audience. The videos also include an adult model interacting with preschool-aged children (one boy [5 years] and one girl [3 years]).
Contacts with intervention	Teachers work with interventionists directly during a 2-hour professional development session before the start of the school year.
Tailoring and targeting	All videos include modeling from a younger [3 year old girls] and older [5 year old boy] model. This allows children at different ages and stages of development to see a model more closely resembling them (tailoring). The videos also include clear verbal instructions for how to practice for each skill could be tailored to suit the needs of the user [see TARGET structure “task” in Table 1].
Self-management	Children are encouraged to monitor their only preferences and current skill levels to engage in the intervention in a meaningful and fun way. [see TARGET structures “Task”, “Grouping” and “Time” in Table 1]
Entertainment	The videos include music and animation as appropriate for a child audience. The in-person sessions that pair with each video are designed for children ages 3–7 years and include age-appropriate and engaging equipment (e.g.., colorful scarves, hula hoops, chalk, etc),
Aesthetics	The videos include color and music as appropriate for young audiences. They also include verbal descriptions and modeling from peers.
Updated information	Teachers will complete a daily facilitation survey. Interventionists will be present at the school four times across the school year (August, October, Feb, and May).
Usability	The videos are all pre-made and ready for use. The corresponding skill stations are predesigned so that all the necessary equipment for each skill is stored in a designated location. Teachers are provided withtwo or three choices of station setups that are possible to use in conjunction with each skill.
Credibility	Schools are provided with an overview pamphlet of the program prior to the start of the school year. This pamphlet includes a list of credentials of the designers of the intervention.
Information architecture	All videos are available through a private YouTube Channel. Participants are allowed to self-navigate through the intervention.
Program exposure	The intervention will be available to the intervention classrooms from October–end of the school year.

The second part of the e:MAP program is the motor activities. Each skill included in the videos has a pre-determined set of two to three possible activities, and the corresponding activities are set up during children’s outdoor recess or free play in a large gym or open space if the weather inhibits outdoor play. Facilitators are provided with all the necessary instructions and equipment to set up all activities. The organization and design of these activities were curated to take less than five minutes to complete all set-up associated with a single session.

#### 2.2.3 Facilitation of MAP

The e:MAP program will be implemented four days a week for 8 weeks (30 min/session, 4 sessions/week, 8 weeks, total 960 minutes). Teachers of classrooms randomly assigned to the MAP condition will facilitate the program. Teachers will be responsible for selecting and playing a session video prior to each gross motor playtime and setting up the corresponding stations. Teachers will also complete a brief survey reporting on the program facilitation (see “2.3.4 Teacher Facilitation”).

#### 2.2.4 e:Health platform

All e:MAP sessions were made available through a private YouTube channel. The full library will be available to teachers the early childhood education centers at the start of the intervention.

### 2.3 Assessments

#### 2.3.1 FMS

We will measure FMS using a battery that yields both process- and product-oriented motor skill scores.

Children will complete the Test of Gross Motor Development, 3rd edition (TGMD-3) [10]. The TGMD-3 is a valid and reliable process-oriented assessment used to measure motor skills in children ages 3 through 10 years. The TGMD-3 measures performance on seven ball skills (1-hand strike, 2-hand strike, dribble, toss, kick, throw, and catch) and six locomotor skills (run, gallop, hop, skip, slide, and jump). Administration and scoring of the TGMD will be done according to the test manual. Children will receive a digital demonstration of the skill before the practice trial [69]. If a child does not understand the specific motor skill during the practice trial, the child will be given a second live demonstration of the skill. All test trials will be coded by an expert coder with >10 years of experience working with the TGMD. Total raw scores for the locomotor subscale (0–44), ball skill subscale (0–56), and total TGMD (0–100) will be calculated.

For five skills- throwing, kicking, standing long jump (SLJ), running, and hopping, we will simultaneously collect product scores. Final scores will include max throwing speed (m/s), max kicking speed (m/s), max jumping distance (cm), max running speed (m/s), and average of max hopping speed on the preferred and non-preferred foot (m/s) [70, 71]. Scores for throwing, kicking, standing long jump (SLJ), and running will be collected from the TGMD-3 test trials [71]. Max hopping speed for the preferred foot will also be assessed from the TGMD-3 test trials, but children will complete two additional hop trials on the non-preferred foot to determine max speed on the non-preferred foot to be used in the final hop score [71].

The final scores used in the main analyses will be the total TGMD raw score, the total summed product score (sum of z-scored product scores) [70]. and a total motor competence score. Motor competence score will be created by standardizing all 13 skills included in the process score (e.g., TGMD-3 skills) and all 5 product scores, adding standard scores, and then scaling from 0 to 100, with 100 representing higher motor competence.

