In conclusion, there is a need for FMS interventions that can be implemented in the absence of a researcher’s presence. e:Health and m:health interventions to promote FMS are an emerging and exciting area of research, and more work is needed to examine how these modalities could be used to deliver FMS and PA interventions in early childhood education settings. This research is particularly needed for children who are at risk for future health disparities, such as children in federally subsidized early childhood education centers serving low-income families. This study addresses this need by creating the e:Motor skills At Playtime (MAP) intervention. e:MAP is an FMS intervention grounded in Achievement Goal Theory and is specifically designed to be implemented through an e:health modality within early childhood education settings. The purpose of this pilot study was twofold. First, we will determine the effects of e:MAP on health outcomes, including FMS and PA, in children who are at risk for future health disparities. Secondly, we will gain insight into the usability and potential sustainability of e:MAP within the early childhood education setting by exploring how teachers perceive the program as well as their ability to facilitate the program.

**Goal 1**: Determine the effects of the MAP e:health program on children’s health outcomes (FMS and PA).**Goal 2**: Explore teachers’ perceptions of and ability to facilitate the MAP e:health program within an early childhood education setting.

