## 2. Materials & methods

### 2.1. Sample

All children enrolled in preschool classrooms at a single Head Start/Great Start Preschool in Michigan will be recruited. Based on initial MAP work [45], we completed a sample size calculation using an alpha level of 0.05 and a desired power of 80% when comparing the two groups to detect an effect size of Cohen’s d = 0.8 [64]. This estimated effect size represents a meaningful change in children’s motor skills and is higher than meta-analytic reports of average effects sizes from motor interventions [18, 22]. The calculation yielded a minimum of 54 children needed (27 per group). To account for 20% lost to follow-up, we will recruit 32 children per group. We will try our best to minimize the loss of follow-up, and this extra recruitment will help us maintain statistical power with any unexpected smaller detectable group differences in the outcome. Due to the nature of research in a school setting, children will be randomized at the level of the classroom. We will recruit from a minimum of 6 classrooms.

To be enrolled, children must meet the following at the time of study enrollment: 3.5–5.0 years old, able to understand simple verbal instructions in English, and be physically capable of completing the motor skills assessment. Children who have a physical or intellectual impairment that would inhibit them from successfully completing the motor skill assessment will be excluded.

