#### 2.3.2 Physical activity

Physical activity will be measured with ActiGraph accelerometers (Actigraph, Pensacola, FL, USA) secured by a hospital band on participants’ non-dominant wrists for one full week (i.e., 5 weekdays and 2 weekend days). The devices will be placed on the child during the school day and set to start recording at midnight. The devices will be removed after seven full days of recording. The devices will be calibrated to collect data at 30 hz, the standard frequency used with accelerometers. Data will be reduced using Actilife software and physical activity behaviors will be determined using cut-points by Johansson et al [72]. The final outcome will be minutes of total and MVPA across the whole day and school day. To be included in the overall physical activity outcome, children will need 3 weekdays + 1 weekend with at least 10 hours of valid wear time[73, 74].

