#### 2.3.4 Teacher facilitation

We will send teachers a daily, 8-question survey asking about their facilitation of the program (see S1 File). We will also ask teachers to take daily photos of the motor skill activities on the provided tablet. This survey plus pictures is a proxy for intervention fidelity. Questions were designed to include 11 of the 12 TiDIER structures[76, 77]. Specifically, the survey includes information on the name of the program, materials, procedures, provider, mode of delivery, where/location, when/how much, tailoring, modifications, planned activities, and actual activities [76, 77]. Primary outcomes of interest will be teacher-reported facilitation as assessed as a percent of sessions and session components fully and correctly executed.

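### Seven overlapping child outcomes are listed without a primary, and the sample size is tied to none of them

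*Protocol article*

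**What the plan says.** **FMS (section 2.3.1).** "The final scores used in the main analyses will be the total TGMD raw score, the total summed product score", followed by a total motor competence score. The third score is made from the ingredients of the other two: "Motor competence score will be created by standardizing all 13 skills included in the process score", plus all five product scores, summed and rescaled to 0–100.

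**PA (section 2.3.2).** "The final outcome will be minutes of total and MVPA across the whole day and school day". Two measures over two time windows make four quantities.

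**Goal 1 (Introduction).** The aim is to determine effects on child health outcomes, naming FMS and PA side by side without an order.

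**Sample size (section 2.1).** The calculation uses alpha 0.05, 80% power and d = 0.8, giving 27 children per group. Of the effect size it says: "This estimated effect size represents a meaningful change in children’s motor skills". No score is named.

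**Analysis (section 2.8).** FMS and PA are both assessed for group differences with mixed models, and an intervention-by-sex interaction is also evaluated.

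**The word primary.** For outcomes it appears once, in section 2.3.4: "Primary outcomes of interest will be teacher-reported facilitation as assessed as a percent of sessions and session components fully and correctly executed". This measure belongs to Goal 2 and is reported as a percentage, not compared between groups.

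**The concern.** The trial has an alpha level, a power target and a stated aim of determining effects. It is therefore set up to give an answer on efficacy, but the article does not say which of seven results gives that answer. If one or two of the seven reach 0.05 and the others do not, nothing in the text says whether the trial found an effect. The sample size does not settle it either, because three different FMS totals all fit the term motor skills. Two things are at stake: the false-positive risk of the Goal 1 conclusion, and whether any single result can be read as the one the trial was sized to deliver.

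**Working it through.** **1. The plan's own figure.** Inputs from section 2.1: d = 0.8, alpha 0.05 (taken as two-sided, since sidedness is not stated), power 80%, equal groups. A two-sample t-test needs 25.5, so 26 per group. At the stated 27 per group, power is 82%. The stated 54 is reproduced to within 2 children. It is a calculation for one test of one outcome.

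**2. Count of outcomes.** FMS: TGMD-3 total, summed product score, motor competence score = 3. PA: 2 measures × 2 windows = 4. Total 3 + 4 = 7.

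**3. Ceiling.** For seven independent tests, the chance of at least one false positive is 1 − 0.95^7 = 0.302. Independence is impossible here. The motor competence score contains the skills and product measures behind the other two FMS totals. The school day lies within the whole day, and MVPA lies within total activity.

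**4. With correlation.** The article gives no correlations, so these are assumptions. The figures come from simulating seven correlated two-sided z-tests at 0.05 with no true effect on any outcome and no allowance for clustering. The last column counts only false positives in favour of e:MAP, where the nominal rate for one test is 2.5%.

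| Assumed correlations | Any false positive | Favouring e:MAP |
|---|---|---|
| Independent (ceiling) | 30% | 16% |
| Composite built from 18 items, weakest overlap tried; PA 0.5; FMS–PA 0 | 25% | 13% |
| Within FMS 0.8, within PA 0.7, across 0.2 | 21% | 11% |
| Composite built from 18 items, strongest overlap tried; PA 0.85; FMS–PA 0.3 | 18% | 9% |
| Within FMS 0.9, within PA 0.9, across 0.4 | 16% | 8% |

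In the two composite rows, the correlation between the motor competence score and the TGMD total comes out at 0.91 and 0.97. This follows from 13 of its 18 components being TGMD-3 skills. If all seven outcomes were correlated at a common 0.8 or 0.9, including FMS with PA, the risk would be 15% or 11%. That requires motor scores and accelerometer minutes to agree as closely as two versions of the same score.

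**5. Can the sample size be traced to one outcome?** Section 2.1 bases it on the earlier MAP study. The Introduction reports that study's motor result as a gain in locomotor skills. The locomotor subscale is calculated in section 2.3.1 but is not one of the three final scores. So the article does not show that d = 0.8 belongs to any of the seven.

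**6. Could all seven stay co-equal?** Bonferroni gives 0.05 / 7 = 0.00714 per test. Power at d = 0.8, ignoring clustering, would be 56% with 27 per group and 66% with 32 per group. About 41 per group would be needed for 80%. Naming one primary keeps that test at 5% and keeps the existing calculation relevant.

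**The case against.** **It is a pilot, all seven outcomes are prespecified, and a multiplicity rule may sit in an analysis plan that is not shown.** The last part stands: the absence of a correction method is no finding. But the choice of primary outcome, and which outcome the sample size serves, belong in the protocol. This article states its outcomes and its sample size explicitly, and the two do not connect. The pilot label lowers the stakes, but the trial still has a powered aim of determining effects.

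**FMS already has some priority.** This is partly right. The phrase about main analyses is applied to the FMS totals only, and the sample size speaks of motor skills. That points to FMS over PA, but three FMS totals remain with no order among them.

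**Stronger readings that the article does not support:**
- A reader might put the risk at 30%, or at 1 − 0.95^14 = 51% by adding seven sex interactions. Both need independence, which the shared data rule out. The interaction asks whether the effect differs between boys and girls and is not another route to an overall claim.
- A reader might infer that the plan allows success to be declared on any one outcome. No such rule is written. The plan leaves the question open.
- A reader might take "Primary outcomes of interest will be teacher-reported facilitation" as making facilitation the trial's primary outcome, in conflict with Goal 1. In its subsection it reads naturally as the main measure from the facilitation survey.
- A reader might say the TGMD-3 total is the only FMS score not standardised on this sample. The article does not state the reference for its z-scores, so that cannot be claimed.

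**Conclusion.** The point holds in a limited form. The article lists seven overlapping child outcomes, names none as primary, and sizes the trial for motor skills without saying which score. The resulting chance of at least one false-positive group difference is roughly 16–25%, or about 8–13% counting only results favouring e:MAP. These figures assume that every outcome is tested at 0.05 two-sided, that there is no true effect on any of them, and that the correlations are as tabulated. The count of seven and the missing primary rest on the text alone. This should be corrected, but it is a matter of designation and does not invalidate the design.

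**What to change.** - **Section 2.8:** name one FMS total as the single primary child outcome, tested at 0.05. The TGMD-3 total raw score is the natural choice: it is listed first, has a fixed 0–100 scale and is not a composite of z-scores.
- **Section 2.1:** state that the sample size serves that outcome, and say which score in the earlier MAP work d = 0.8 came from, if any. The text should not imply that it came from the TGMD-3 total unless it did.
- **Sections 2.3.1, 2.3.2 and 2.8:** label the other two FMS totals, the four PA outcomes and the sex interactions secondary or exploratory. Report them as estimates with 95% confidence intervals, without a stand-alone claim of effect.
- **Section 2.3.4:** call facilitation the primary implementation outcome, under Goal 2.

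The cost is a few sentences, with no change to data collection or recruitment. The downside is that a significant PA or product-score result alone can no longer be the headline.
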